### Sample size using power calculation

CGM data provide numerous metrics to offer unique insight into variations and deviations of glucose levels over time—area under the curve (AUC), mean glucose, coefficient of variation of glucose, mean amplitude of glucose excursions (MAGE) and time in range (TIR).^14^ Additionally, there is no current evidence regarding the effect of diet composition and glycaemic load on metrics of CGM in pregnant women with diabetes throughout the duration of pregnancy. Therefore, we have elected to focus on AUC as the primary metric because it is easily interpretable and commonly used to quantify postprandial glycaemia. Evidence from Fabricatore e*t al*^15^ demonstrated a significant association (p<0.05) between self-reported GI and measures of CGM (including AUC, mean glucose and % time hyperglycaemic) in a clinical trial of 21 women and 5 men with type 2 diabetes. Assuming similar effect sizes between GI (per unit) and AUC glucose (β=0.36 mg/dL/min; R^2^=0.38), mean glucose (β=0.02 mol/L; R^2^=0.38) and time spent >10 mol/L blood glucose (β=0.41%; R^2^=0.36), we will have sufficient power (power=0.90) to detect a significant pairwise effect of GI on these parameters with 63 participants. Another study by Law *et al* suggested that this will provide sufficient power (power=0.90) to compare subgroups of participants (stratified by body mass index (BMI), age, type of diabetes) and test for significant differences (of a minimum effect size) in AUC glucose (±61 mmol/L/min), mean glucose (±0.5 mmol/L) and % time hyperglycaemic (±3.7%).^16^ Finally, given the comparable proportions of women reported to be of white European versus non-white European ancestry (57% vs 43%) or diet versus diet+medication (46% vs 54%), we also anticipate having adequate power to compare these confounders of glycaemic response. To account for attrition, we will increase our recruitment target by 20% above our calculated, suggesting a target sample size of 76 recruited women. We have allocated ~6 months to recruit 76 women (at 10–12 weeks’ gestation) and ~15 months for study completion (ie, final delivery). All power analyses were performed using G*Power (V.3.1).^17^

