#### Outcomes of interest

The primary outcome of interest is CGM glucose data, with AUC glucose as the primary CGM metric of interest. Secondary outcomes of interest are associations between metrics of dysglycaemia during pregnancy with maternal outcomes (e.g., gestational weight gain, pre-eclampsia, hypertension, mode of birth, birth trauma, preterm delivery and metabolism) and infant outcomes (e.g., birth weight, height, preterm delivery, mortality, birth trauma, hypoglycaemia, congenital malformation, head and abdominal circumference, perinatal morbidity), and the moderating effects of genetics, metabolism, and diet and lifestyle. All secondary analyses are considered exploratory.

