### Statistical analysis considerations

All standard CGM metrics will be calculated, with AUC glucose as the primary CGM metric (mean±SD). The primary analysis will be the effect of dietary protein on AUC glucose for the 24-hour window immediately after each study meal. The analysis will be constructed as pairwise linear model with study meal (0=low protein, 1=high protein) regressed against 24-hour mean AUC glucose and adjusted for study parameters (e.g., randomised meal order) and participant covariates (e.g., maternal age, ethnicity, parity, BMI, gestational age, physical activity and sleep quality). Statistical significance will be set at p<0.05, where a p<0.05 for study meal will suggest a significant effect of dietary protein on 24-hour postprandial AUC glucose. The direction and significance of covariates will be investigated to identify study and participant mediators of the association. Statistical analysis will be conducted in R studio and SPSS (Ver. 29+).

Secondary research objectives include (1) the association between dysglycaemia and maternal and newborn health, and (2) the association between maternal diet in early pregnancy with dysglycaemia during pregnancy. These analyses will also be performed using regression models adjusted for covariates, with the assessment of early diet on longitudinal changes in dysglycaemia also adjusted for time points of AUC (i.e., mixed-model). The association between early maternal diet and AUC will be performed using three distinct dietary metrics (calculated from myFood24):

1. Overall diet quality

The association between diet quality and dysglycaemia will be assessed using an overall diet quality score.^24^ This scoring method has been modified and used previously to assess maternal diet quality in a multiethnic prospective birth cohort.^25^ The modified Alternative Healthy Eating Index (mAHEI) score is calculated using the following method; an individual will receive 10 points for each of the following food categories when they consume above or below a threshold of: ≥5 servings of vegetables, ≥4 servings of fruits, ≥1 serving of nuts or soy proteins, ≥3 servings of whole grains, a ratio of ≥4 servings of fish to 1 serving of meat and eggs, and ≤0.5 servings of less-healthy foods (i.e., fried foods and processed meats). Intermediate intake is scored proportionally between 0 and 10. The maximum mAHEI score is 60; the higher the score, the more healthful the participant’s diet.

2. Macronutrient

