Daily macronutrient consumption (total carbohydrates, proteins and fats) and markers of GI quality (fibre, sugars) will be adjusted for energy and regressed against CGM measures of dysglycaemia. Doing so will allow for the contribution of individual macronutrients on glycaemic measures to be evaluated.

3. Cardinal foods

Partial least squares will be used to identify foods that are more commonly observed in participants with favourable or unfavourable glycaemic control (identified above/below median for glycaemic measures). These foods will then be investigated for their association with measures of dysglycaemia using a regression model.

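### The exploratory cardinal-foods screen cuts continuous CGM measures at the sample median before partial least squares, which needlessly lowers the chance of finding related foods

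*Protocol article*

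**What the plan says.** The point concerns the third of three dietary analyses under Statistical analysis considerations in the protocol article, headed Cardinal foods. It has two steps.

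- **Screen.** Partial least squares picks out the foods that occur more often in women with "favourable or unfavourable glycaemic control (identified above/below median for glycaemic measures").
- **Follow-up.** "These foods will then be investigated for their association with measures of dysglycaemia using a regression model". Only the foods that the screen picks go forward, and no cut of the outcome is stated here.

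The macronutrient analysis just before it takes the intake variables, which "will be adjusted for energy and regressed against CGM measures of dysglycaemia", again with no cut stated. The measures named elsewhere in the article are AUC, mean glucose, coefficient of variation, MAGE and time in range. All are continuous, and AUC is the primary one: "All standard CGM metrics will be calculated, with AUC glucose as the primary CGM metric (mean±SD").

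Under Outcomes of interest the article sets the status of this work: "All secondary analyses are considered exploratory".

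**The concern.** A median split replaces each woman's glucose value by one of two labels. Women just either side of the median become opposites, and women far apart on the same side become identical. The median is a property of whoever enrols, not a clinical threshold. The method does not need the split, because partial least squares takes one or several continuous outcomes.

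What is at stake is the list of candidate foods. Detection is the purpose of an exploratory screen, and coarsening the outcome weakens detection. The later regression cannot bring back a food that it never receives.

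**Working it through.** **Inputs from the article.** The evaluable sample is 63 women (Sample size using power calculation). Adding 20% gives 63 × 1.20 = 75.6, so 76, which matches the recruitment target. Significance is at 0.05, taken as two-sided. The article gives no sample size, power or information figure for the food screen, so there is no figure of its own to reproduce for this step.

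**Assumptions of this check.** Food–glycaemia correlations of 0.20 to 0.40; 50 independent foods, 5 of them truly related; various shapes for the glucose measure. None of these is in the article.

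**1. Information kept, normal measure.**
- Splitting a normal variable at its median multiplies a correlation by √(2/π) = 0.798.
- Information kept is 2/π = 0.637, so the loss is 1 − 0.637 = 0.363, about 36%.
- Effective size is 63 × 0.637 = 40.1 women.

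**2. Power for one food, n = 63.** Fisher z: power ≈ Φ(atanh(r) × √(n − 3) − 1.96), with √60 = 7.746.
- Continuous, r = 0.30: 0.3095 × 7.746 − 1.96 = 0.437, so power is 0.67.
- Split, r = 0.30 × 0.798 = 0.239: 0.2441 × 7.746 − 1.96 = −0.069, so power is 0.47.
- The same sum at r = 0.40 gives 0.91 against 0.73.
- Simulation at r = 0.20 gives 0.35 against 0.23.
- Sample size for 80% power at r = 0.30, from ((1.96 + 0.842)/atanh(r))² + 3: 85 continuous, 135 split.

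**3. Simulated screen.** One partial least squares component, 50 foods, 5 real, r = 0.30 each, normal measure. VIP is variable importance in projection.

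| | Continuous | Split |
|---|---|---|
| Real foods with VIP > 1 | 89% | 79% |
| Unrelated foods with VIP > 1 | 22% | 25% |
| Real foods among the top 5 | 64% | 50% |

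**4. Other outcome shapes.** Per-food power by simulation, n = 63, r = 0.30.

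| Measure | Raw | Split | Log | Rank |
|---|---|---|---|---|
| Log-normal, σ = 0.5 | 0.63 | 0.48 | 0.68 | 0.65 |
| Log-normal, σ = 1 | 0.51 | 0.48 | 0.68 | 0.65 |
| t errors, 5 df | 0.69 | 0.62 | – | 0.75 |

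A median split gives the same two groups whether or not the measure is first transformed, so skewness cannot help it. Skewness only hurts an untransformed continuous analysis. The better transformed option beats the split by 0.68 − 0.48 = 0.20 in the log-normal cases and by 0.75 − 0.62 = 0.13 with t errors.

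**The case against.** The strongest reply is that the size of the loss is a modelling assumption. The article gives no distribution for any CGM measure, and some, such as time in range, are bounded and may be skewed. Against a raw, strongly skewed measure the split costs little (0.51 against 0.48), and with 5-df t errors the theoretical loss is only about 4%. A split does protect against outliers. This stands in part: 36% is a normal-theory figure, and a proposal that ignored transformation might gain almost nothing. It does not rescue the split, because a log or rank transform gives the same protection and keeps the ordering within each half.

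Two further replies stand.

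- **The assumed effects are generous.** Five independent foods at r = 0.30 explain 5 × 0.09 = 45% of the variance, more than the R² of 0.38 that the article cites for glycaemic index. At r = 0.20 (20% of variance) the screen is weak either way: 40% against 30% of real foods in the top 5.
- **The rules used to score the screen are this check's own.** The article states no per-food test, VIP cut-off or top-5 rule.

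A reader might infer that the split discards 36% of the information as a fact about this trial, that it brings no benefit at all, or that it makes the screen miss real foods. The documents support none of these. They support a lower chance of finding such foods, by an amount that depends on the shape of the measure.

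A reader might also object that a woman can be favourable on one measure and unfavourable on another. That is equally true of continuous measures and is not an argument against the split. Nor is it a fault that a condensed article gives no reason for the split. The point rests on the rule that it states.

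**Conclusion.** The point holds as a cheap improvement of low severity. The article states a median split that partial least squares does not need and that the neighbouring macronutrient analysis does not state. With a near-normal measure the loss is up to about 36% of the information. At an assumed correlation of 0.30 that means per-food power of about 0.47 instead of 0.67, and about 79% instead of 89% of truly related foods passing VIP > 1. For skewed or heavy-tailed measures the advantage over the split depends on choosing a suitable transform. In the cases tested, a log- or rank-transformed continuous measure was always better.

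The consequence is confined to which foods reach the follow-up regression in one of three exploratory dietary analyses. The primary meal comparison, the diet-quality analysis and the macronutrient analysis are untouched.

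**What to change.** Replace the two-group label in the screen with the continuous measure. Suggested wording: *Partial least squares regression of continuous AUC glucose and, jointly, the other continuous CGM measures on food intakes will be used to identify foods associated with glycaemia. Measures that are skewed will be log- or rank-transformed, by a rule fixed before the analysis. Groups above and below the median will be used only in descriptive tables.*

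The cost is one sentence of analysis text, with the same women, data and family of methods. There are two downsides. The food list is no longer a simple contrast of two groups, and a transformation has to be chosen in advance.

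### The exploratory cardinal-foods analysis selects foods on glycaemic control and then relates them to glycaemia in what appears to be the same cohort, so second-step estimates and any p-values will be too optimistic

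*Protocol article*

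**What the plan says.** The protocol article, under *Statistical analysis considerations*, announces the diet analyses as follows: "The association between early maternal diet and AUC will be performed using three distinct dietary metrics". The third of these, *Cardinal foods*, has two steps.

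- Selection: "Partial least squares will be used to identify foods that are more commonly observed in participants with favourable or unfavourable glycaemic control". The groups are "identified above/below median for glycaemic measures".
- Follow-up: "These foods will then be investigated for their association with measures of dysglycaemia using a regression model".

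The only women described are the trial's own participants. *Sample size using power calculation* gives the recruitment target, "suggesting a target sample size of 76 recruited women", and the number on which power rests: "we will have sufficient power (power=0.90) to detect a significant pairwise effect of GI on these parameters with 63 participants". The article mentions no second cohort and no division of the sample. *Outcomes of interest* labels all secondary analyses exploratory. The only significance threshold in the article, "Statistical significance will be set at p<0.05", stands in the paragraph on the primary analysis.

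**The concern.** The first step keeps foods because they vary with glycaemia in these women. The second step asks whether the kept foods vary with glycaemia. If the women are the same, the answer is partly settled by the selection. A food that differed between the groups by chance carries that chance difference into the regression. Its coefficient is then biased away from zero, and the usual standard error and p-value take no account of the selection.

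This is a property of the stated order of steps, not of a missing detail. What is at stake is limited but real. The *Discussion* says that identifying dietary mediators of glucose variability will help to develop strategies for controlling glucose in this population. Named foods that seem to be confirmed by a second step could be taken further than the data allow.

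**Working it through.** The article gives no figure for this analysis, so there is none to reproduce. The check is a simulation in which no food is related to glucose.

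**Inputs from the article.** 63 women; a median split for selection; the selected foods regressed on dysglycaemia; 0.05 as the only stated threshold (taken as two-sided).

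**Assumptions.** 30, 50 or 100 candidate foods; independent normal intakes; one partial least squares component; the ten foods with the largest absolute weight carried forward; each food tested singly against continuous glucose without covariates. There were 1,500 runs per setting.

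**Procedure.**

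1. Let g = 1 if a woman's glucose y is above the median, otherwise 0. With standardised intakes X, the first component's weights are w ∝ X′(g − mean g), so ranking foods by |w| is ranking them by |correlation with g|.
2. For normal y, the correlation of g with y is √(2/π) = 0.80. Selecting on the split is therefore close to selecting on y itself.
3. Each selected food is tested with t = r√((n − 2)/(1 − r²)) on n − 2 degrees of freedom, where r is its correlation with the tested measure.
4. Three versions of the second step were run: the same measure y; a different measure, 0.7y + √(1 − 0.49)·e, which correlates 0.7 with y; and the same measure with selection in one half of the women and testing in the other half.

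**Share of tested foods with p<0.05 (nominal 5%), 63 women, top ten foods**

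| Candidate foods | Same measure | Measure correlated 0.7 | Separate halves |
|---|---|---|---|
| 30 | 13.6% | 9.4% | 5.0% |
| 50 | 20.2% | 12.2% | 5.0% |
| 100 | 30.5% | 17.0% | 5.3% |

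Repeat runs of the same-measure setting gave 13% to 14%, 19% to 20% and 30% to 32%.

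**Chance of at least one such food in a study, same setting**

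| Candidate foods | Same measure | Measure correlated 0.7 | Separate halves |
|---|---|---|---|
| 30 | 74.3% | 63.4% | 40.0% |
| 50 | 88.5% | 71.1% | 39.8% |
| 100 | 96.9% | 83.7% | 41.7% |

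The comparator for the second table is not 5%. Ten independent foods chosen in advance give at least one hit in 1 − 0.95¹⁰ = 1 − 0.599 = 40% of studies, as the separate-halves column confirms. The excess over 40% is the part due to re-use of the data.

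**Plausibility check.** Under the null, 0.05 × p of the p candidate foods are expected to reach p<0.05. With ten tested, the per-food rate cannot exceed 0.05p/10, which is 15%, 25% and 50% for 30, 50 and 100 foods. The simulated 13.6%, 20.2% and 30.5% lie below these limits.

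**Sensitivity, same measure.** Carrying forward five foods gives 22.5%, 28.6% and 41.7%. Selecting foods whose variable importance in projection exceeds 1 gives 14.3%, 14.6% and 14.3%. With intakes correlated 0.3, rates were still 13% to 28%. With 76 women and ten foods, they are 13.6%, 19.6% and 30.1%.

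**The case against.** Several points can fairly be made in the plan's favour.

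- **Exploratory status.** The analysis is one of three dietary metrics under a secondary objective, and it is labelled exploratory. This stands and lowers the importance of the point. It does not remove the bias in the coefficients.
- **The same measure in both steps.** A reader might infer this, but the text does not say so. It selects on glycaemic measures and then relates foods to measures of dysglycaemia. The article lists several (AUC, mean glucose, coefficient of variation, MAGE, time in range) and has more than one time point. The measures may therefore differ. At a correlation of 0.7 the inflation is about 9% to 17%; at 0.5 it is about 7% to 11%. It shrinks but stays above 5%.
- **Promised p-values.** A reader might infer that invalid p-values are planned. The article ties its threshold to the study meal in the primary analysis and promises none here. The statement about p-values is therefore conditional; the bias in the coefficients is not.
- **Near-certain false findings.** A reader might infer that the step almost always produces a significant food because of circularity. The documents do not support this. They give neither the number of foods nor the selection rule, the chance with 30 foods is about 74%, and about 40% arises from testing ten foods at all.
- **The median split.** A reader might call it an error. It discards information, but it is a legitimate way to describe which foods are commoner in each group.
- **A fuller plan may exist.** Component number, selection rule and validation scheme are commonly left to an analysis plan, and their absence is not held against the article. What remains is the stated two-step order. The simulation also omits the covariate adjustment that the article intends and the sparse, skewed intakes likely in three-day records. Its exact figures are therefore illustrative.

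**Conclusion.** The point holds as a limited one. As written, and with only one cohort described, the second step re-uses the information that selected the foods. Food coefficients will be biased away from zero, and any p-values or intervals attached to them will be too optimistic.

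Under the stated assumptions, the per-food false-positive rate is about 13% to 31% with the same measure in both steps and about 9% to 17% with a measure correlated 0.7, against 5%. The chance of at least one hit is about 75% to 97% in the same-measure case, against about 40% from multiplicity alone. The size depends on the assumed number of foods and the selection rule; the direction was the same in every setting tried. The return to about 5% with separate halves shows that the shared data are the cause.

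The randomised meal comparison, its sample size and its significance test are not affected.

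**What to change.** Change the second step of the cardinal-foods analysis as follows.

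1. Nest food selection and estimation together inside repeated cross-validation, so that performance is always measured in women who did not contribute to the selection.
2. Judge the whole procedure by one permutation p-value. Permute each woman's set of glycaemic measures as a block and re-run the selection in every permutation.
3. Report food-level coefficients as descriptive, without post-selection p-values.

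A single split into halves also restores the per-food error rate, but with 63 women it leaves 31 for one step and 32 for the other, and several foods would still be tested.

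Optionally, use the continuous glycaemic measure in the partial least squares step instead of the median split. This is a gain in efficiency, not the correction of an error.

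The cost is some analyst time, with no new data and no added burden on participants. The downside is that fewer foods will be called significant.

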### Quality control

All participants will receive standard clinical care as per NICE guidance, which will minimise researcher bias. The primary outcome measures are based on laboratory measurements and predetermined cut-off values, which the researchers will not be able to influence. We do not foresee significant researcher bias in collecting antenatal and perinatal outcome data because these will be obtained by clinical staff who are independent of the study outcome and from the participants’ medical records. We do not foresee any significant researcher bias in collecting lifestyle records, as standardised and validated questionnaires will be used to obtain this information. Furthermore, all participants will be asked to consume the two standard meals but the order of their consumption will be randomised. We do not foresee any conflict of interests. The data collected will not be used for informing clinical care decisions of specific cases; all the women will continue with their usual clinical care pathway for the duration of their pregnancy, and all women will be free to terminate their participation in the study at any time with no effect on their quality of care.

### Ethics approval

This study has been reviewed and approved by the Leeds East Research Ethics Committee at the University of Leeds (21/NE/0196).

